### Analysis Plan

The cluster randomized trial design will be used by randomizing primary care physicians (PCP) into the intervention or usual care arms. Outcomes will be collected and analyzed at the patient level. We will examine assigned randomization against the computer-generated randomization scheme to ensure randomization validity. Patient characteristics between the two groups will be compared using mixed effects models for continuous variables and generalized estimating equations for categorical variables while adjusting for random PCP effects. We will examine the distributions of continuous variables and use alternative approaches such as transformation or nonparametric methods in cases of violation to the normal distribution assumption. We will also examine the frequency distribution of all categorical variables and adopt exact inference procedures in cases of zero or small cell size. Any baseline variable that is found to be significantly different between the two groups will be included as a covariate in the analyses outlined below.

An intension to treat approach will be used in the analysis of all outcome measures. Composite cognitive scores collected at 6, 12, 18 and 24 months will be used as the primary outcome variables in mixed effects models. An indicator variable for intervention group (intervention vs usual care), time, interaction between group and time, and baseline cognitive scores will be included as independent variables as well as significant factors from the baseline comparison. PCP will be used as random effects to adjust for within-physician correlations. Significant group and time interaction or significant group main effect will indicate differences in cognitive function between the two groups. If significant interactions between group and time are found, post-hoc analyses will be conducted to determine the times when the two groups have significantly different cognitive scores. A significant main group effect in the absence of a group-by-time interaction would indicate differences between groups in cognitive function at all follow-up time points.

In a second set of models, we will determine whether differences between groups were accounted for by decreases in total exposure to anticholinergics from baseline to 24 months. For each medication, standardized daily exposure will be calculated using standardized daily dose as in the study by Gray^7^ and validated in our prior work^14
17

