### Sample Size and Rationale

The sample size calculation was conducted using a mixed effects model and adjusting for the cluster randomization design. Assuming a within-subject correlation of 0.3, 0.2 and 0.1 for outcomes observed 6, 12 and 18 months apart, respectively, from the same individuals over time, 96 patients per group is required for 80% power to detect differences in composite cognitive scores of 0.6 SD at 24 months between the intervention and usual care groups with type I error rate at α=0.05 assuming linear trends in cognitive change in both groups. We further assume an intra-class coefficient (ICC) of 0.05 for primary care physicians and an average of 6 patients per physician. Accounting for the cluster design requires 120 patients per group to complete the trial. With an expected 30% attrition rate, we plan to enroll 172 patients per group into the study. Prior studies have reported mean differences in 1-year change of cognitive scores of 1.82 (SD 17) or 1.93 (SD 15) between those on definite anticholinergics versus those non-users. The effect sizes we used assume that our intervention will be able to detect a one-sixth reduction in expected cognitive decline if patients in the intervention group discontinue anticholinergics. Our assumption on the ICC is based on prior studies on prescribing patterns in physicians and practices.^58^

In Primary Aim 2, using the effective sample size of 96 patients per group accounting for the design effect from cluster randomization, we will have 85.6% power to estimate the confidence bands with half-width of 0.3 SD for the differences in symptom scores from PROMIS and HUI scores between the intervention and usual care groups during follow-up using the two-sample t-tests at the 0.05 level. Power estimates were calculated using the GLMPower and Power procedures in SAS software version 9.4 (SAS Institute, Cary, North Carolina).

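### The 85.6% precision figure for PROMIS and HUI uses patient-level degrees of freedom; for the comparison it names, the plan's inputs give about 61% to 80%, depending on how many physicians there are

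*Protocol article*

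**What the plan says.** All the inputs stand in Sample Size and Rationale. For the primary outcome it arrives at 96 patients per group before clustering and assumes an "intra-class coefficient (ICC) of 0.05 for primary care physicians and an average of 6 patients per physician". It then says "Accounting for the cluster design requires 120 patients per group to complete the trial", and "With an expected 30% attrition rate, we plan to enroll 172 patients per group into the study".

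For PROMIS and HUI it works "using the effective sample size of 96 patients per group accounting for the design effect from cluster randomization". It states that "we will have 85.6% power to estimate the confidence bands with half-width of 0.3 SD for the differences in symptom scores", obtained "using the two-sample t-tests at the 0.05 level".

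Randomization procedures allocates primary care providers, not patients, 1:1. The Analysis Plan says PROMIS and HUI will be compared in the same way as the cognitive scores: mixed models of the 6-, 12-, 18- and 24-month values with group, time, their interaction and the baseline score. In those models "PCP will be used as random effects to adjust for within-physician correlations". The number of physicians is not stated.

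**The concern.** A probability that an interval is no wider than a given limit depends on two things: the expected standard error, and how much the estimated standard error varies from trial to trial. Dividing by the design effect deals with the first. The second is governed by degrees of freedom. When physicians are randomised and carry a random effect, the standard error of the arm contrast comes from variation between physicians, of whom there are far fewer than patients. Entering 96 as though it were a count of independent patients therefore makes the standard error look more stable than it will be.

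This is the only numerical operating characteristic that the article gives for the quality-of-life and safety aim. The trial withdraws drugs used for depression, anxiety, insomnia and pain, and readers will use these intervals to judge whether symptoms worsened. As printed, the risk of missing the stated precision is about 1 in 7. If the figure is too high, so is that assurance.

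**Working it through.** **Inputs** (Sample Size and Rationale): effective n = 96 per arm; ICC 0.05; 6 patients per physician; 120 completers and 172 enrolled per arm; half-width limit 0.3 SD; two-sided 95% interval; SD set to 1.

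**Formula.** Half-width = t(0.975, df) × s × SE, where SE = √(2/n_eff) and df × s² follows a chi-square distribution on df. Then P(half-width ≤ 0.3) = P(χ²_df ≤ df × [0.3/(t × SE)]²). The version given coverage also requires that the interval contains the true difference.

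**1. The printed figure.** SE = √(2/96) = 0.1443. With df = 2 × 96 − 2 = 190, t = 1.973 and the half-width at s = 1 is 0.285. The probability is P(χ²₁₉₀ ≤ 210.96) = 85.8%, or 85.56% given coverage. The second matches the printed 85.6%.

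**2. Number of physicians, completer reading.** The design effect is 1 + 5 × 0.05 = 1.25, and 96 × 1.25 = 120 completers. The plan's own inflation thus applies cluster size 6 to completers, so 120/6 = 20 physicians per arm and df = 2 × 20 − 2 = 38.

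**3. Same variance, physician-level df.** With df = 38, t = 2.024 and the half-width at s = 1 is 0.292. The probability is P(χ²₃₈ ≤ 40.06) = 62.1%, or 61.1% given coverage. A simulation of 20 × 6 patients per arm at ICC 0.05, with the physician variance truncated at zero, gives 62.3%. The half-width reached with 85.6% probability is 0.326 SD. Combining a patient-level critical value with the clustered standard error gives 71%.

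**4. Enrolled reading.** If the 6 are enrolled patients, 172/6 ≈ 28.7 physicians per arm. With 120 completers:

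| Physicians per arm | Completers each | Design effect | n_eff | df | P (given coverage) |
|---|---|---|---|---|---|
| 20 | 6 | 1.25 | 96 | 38 | 62.1% (61.1%) |
| 28 | 4.29 | 1.164 | 103.1 | 54 | 79.5% (79.0%) |
| 29 | 4.14 | 1.157 | 103.7 | 56 | 81.1% (80.6%) |

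**5. What the planned model could add.** These are unconditional probabilities with 20 physicians per arm and 38 df. The correlations are assumptions, because the article gives none for PROMIS or HUI.

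- Baseline adjustment at a single visit multiplies SE by √(1 − r²). At r = 0.2 / 0.3 / 0.4 / 0.5 this gives 69% / 77% / 87% / 95%.
- Averaging four visits with exchangeable correlation ρ gives a patient-level variance of (1 + 3ρ)/4. Holding the physician variance at 0.05, SE² = (2/20) × [0.05 + ((1 + 3ρ)/4 − 0.05)/6].

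| ρ | Variance of four-visit mean | SE | Half-width at s = 1 | P(half-width ≤ 0.3) |
|---|---|---|---|---|
| 0.5 | 0.625 | 0.121 | 0.244 | 98% |
| 0.6 | 0.700 | 0.126 | 0.255 | 94% |
| 0.7 | 0.775 | 0.131 | 0.265 | 89% |
| 0.8 | 0.850 | 0.135 | 0.274 | 81% |

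**The case against.** The best defence is that the sentence is openly an approximation. It names an effective sample size and a two-sample t method, and 85.6% follows correctly from those. The planned analysis is a different and more efficient one. It uses four follow-up visits and the baseline score, and the sentence itself speaks of differences over follow-up. If the within-subject correlations given for cognition (0.3, 0.2 and 0.1 at 6, 12 and 18 months apart) are borrowed, the four-visit mean has variance (4 + 2 × (3 × 0.3 + 2 × 0.2 + 0.1))/16 = 0.425. The expected half-width is then 0.215 SD and the 0.3 SD limit is almost certain to be met. The physician count is also an inference, and the enrolled reading leaves a gap of only about 5 to 7 points.

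Much of this stands. A reader might infer that the trial will deliver only 61% for its PROMIS and HUI comparisons, or that the claim survives only with baseline adjustment at a correlation of about 0.4 or more. The documents support neither. The first figure belongs to an unadjusted, single-visit comparison, and the second inference ignores averaging over visits. Nor would it be fair to say that the intervals will be materially too wide. The expected half-width moves from 0.285 to 0.292 SD, and the half-width assured at 85.6% moves from 0.30 to about 0.33 SD, which is 3.0 to about 3.3 points on the PROMIS T-score (10 points per SD).

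What does not stand is the printed number as a property of the comparison it names. An effective sample size does not carry 190 degrees of freedom in a provider-randomised comparison, and neither reading of cluster size reaches 85.6% on the stated t basis. A more efficient analysis may justify that figure or a better one, but the article does not make that calculation.

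**Conclusion.** The point holds, and it is minor. The 85.6% is what 192 independent patients would give. For the single-visit, unadjusted t comparison, provider randomisation gives about 61-62% with 20 physicians per arm, or about 80% with about 29. The lower figure rests on the plan's own step from 96 to 120, which applies 6 per physician to completers. The higher one rests on reading 6 as enrolled patients. Both assume ICC 0.05 for these outcomes, equal cluster sizes and physician-level degrees of freedom. Under the planned repeated-visit model the true figure may lie on either side of 85.6%: with four visits averaged and 38 df, the crossing is at a visit correlation somewhat above 0.7. The effect is on the assurance attached to the half-width and hardly at all on the expected half-width, which stays below 0.3 SD. The cognitive primary outcome is not touched.

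**What to change.** In Sample Size and Rationale, recompute the figure for the analysis actually planned: the mixed model with baseline score, physician random effect and physician-level degrees of freedom. State the number of physicians per arm, whether the contrast is at one time point or averaged over visits, and the assumed baseline and visit correlations for PROMIS and HUI. If the two-sample t basis is kept instead, restate the figure as about 61% (20 physicians per arm) to 80% (29 per arm) and label it single-visit and unadjusted. Printing 61% alone, without that label, would understate the precision of the planned comparison.

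The cost is one recalculated number and a sentence of assumptions. Enrolment, conduct and the primary analysis stay as they are.

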### Ethics Review and Approval

All procedures have received and maintained ethical approval from the Institutional Review Board of the Indiana University (IRB# 1811254189; Federal-Wide Assurance Number, FWA00003544). As a multisite clinical trial, a reliance agreement was established to retain the Indiana University IRB as the single site ethical review board. The trial has also been registered at clinicaltrials.gov (Identifier: NCT04270474).

The study employs an external DSMB including a senior investigator trained in geriatrics (chair), a biostatistician, a pharmacist/pharmacy services researcher, and funding agency representatives. The DSMB approved the study procedures meets at 6–9 month intervals or as needed to review safety data.

The study received approval to initiate recruitment in March 2020 just days before a national interruption of research activities as a result of the global pandemic. In response, the study team revised operations to shift to fully remote procedures to avoid further delay in initiating and executing the trial. This included revisions to the process for recruitment, data collection, and measures employed. In June 2020, these changes were approved by the IRB, the DSMB, and the National Institute on Aging (NIA), with recruitment starting in July 2020.

## Discussion

The R2D2 study will be the first to evaluate the impact of deprescribing strong anticholinergic medications on measures of cognition captured up to two years following the deprescribing attempt. Key elements of the study design include cluster randomization to minimize risk of contamination and a two year follow up phase to evaluate the impact of deprescribing on long-term cognition. The deprescribing intervention utilizes a pharmacist-based deprescribing care coordinator approach to reduce the use of potentially inappropriate anticholinergic medications in primary care older adults. This study will advance the field by addressing the potential causal relationship between anticholinergic medication use and cognition.

In addition to these key features, we note that our approach to the deprescribing intervention intends to test the hypothesis that anticholinergic medications adversely affect cognitive performance. Therefore, the intervention offers alternative, non-anticholinergic medications as alternatives where preferred by participants in the intervention arm. This is not to be confused with other deprescribing approaches that may attempt to reduce the total number of medications (polypharmacy in general). While the intervention does offer a tapered discontinuation without replacement of an alternative medication if acceptable to the participant, it is possible the net impact on the total number of medications will be nil.

We recognize other prospective anticholinergic deprescribing trials that have been conducted, including studies by Moga and colleagues,^30^ Ailabouni and colleagues,^29^ Kersten and colleagues,^26^ and Gnjidic and colleagues.^28^ These studies were important preliminary work that either proved feasibility or guided deprescribing approaches in anticholinergic deprescribing, however only the study by Moga and colleagues identified the potential for improvement in executive function in a subgroup of participants with a higher level of amyloid-beta pathology. Other studies failed to find differences in cognitive outcomes, though three were preliminary studies limited by sample size, one was limited by frailty of the study population or duration of follow-up. Our approach is unique in its exclusive focus on strong anticholinergic medications, target population of primary care older adults without dementia, and duration of follow-up. Additionally, our planned sample size of 344 represents the largest randomized trial of anticholinergic deprescribing conducted to date.

Some limitations of the study are worth noting. First, while the cognitive outcomes employed in this study represent domains relevant to the diagnosis of dementia, we recognize that performance on cognitive outcomes alone is only one component of the diagnosis of dementia. If our hypotheses hold, and a differential effect on cognition between groups is identified, future work could extend the intervention and determine the impact on the diagnosis of dementia and time to diagnosis of dementia. Secondly, the study as proposed lacks a measure of the mechanism through which the causal relationship between anticholinergics and cognition are linked. While financial and scientific support for the planned trial is acknowledged, the resources were insufficient to include biomarkers of the mechanism through which anticholinergics may lead to cognitive impairment. We are unable to include biomarkers of anticholinergic use and cognitive impairment to correlate changes is measures of medication use with brain health. Finally, we collect two sources of medication use: self-reported medication use at six month intervals and medication prescriptions (orders) from the electronic medical records. These sources introduce advantages and disadvantages, however represent the data sources available to the study team throughout the conduct of the study.

### Trial Status

The study began recruitment on July 20^th^, 2020 and is currently recruiting participants. At the time of drafting of the manuscript, approximately 328 participants have been enrolled and is expected to be completed by July 31^st^, 2024. Data collection is expected to be completed by July 31^st^, 2026.

## Figures and Tables

**Figure 1 F1:**
[figure not shown]
Conceptual Model of the R2D2 Trial

**Figure 2 F2:**
[figure not shown]
Overview of the cluster randomized design and outcome assessments

**Figure 3 F3:**
[figure not shown]
Schedule of enrollment, interventions, and assessments. *See Table 1 for list of variables and outcomes to be collected at each time point.

**Figure 4 F4:**
[figure not shown]
Factors to be influenced by the Pharmacist Deprescribing Care Coordinator

**Table 1: T1:** Planned Outcome Measures and Covariates

Variables/Outcomes	Baseline	6 Months	12 Months	18 Months	24 Months	Method
Demographic characteristics	X					Self Report

Clinical characteristics/Diagnoses	X				X	Self Report & EMR

Self-Reported Medications	X	X	X	X	X	Self Report

Prescribed Medications	X				X	EMR

Cognitive Performance	X	X	X	X	X	Performance

PROMIS 4-item scales:	X	X	X	X	X	Self Report
• Pain						
• Anxiety						
• Insomnia						
• Depression						

Health Utility Index	X	X	X	X	X	Self Report

ApoE 4	X					Saliva

ApoE 4: Apolipoprotein 4

EMR: Electronic medical record

PROMIS: Patient Reported Outcome Measurement Information System

## Data Availability

Data will be made available upon written request, including information about the identity of the investigator(s), data requested and plans for data analysis. Trial results will be shared on clinicaltrials.gov, published in peer-reviewed scientific publications and presented at state, regional, national, and possibly international scientific meetings.
